#### Educational Booklet

Patients randomised to the booklet arms of the trial will receive a copy of "Your Back operation"[55] on discharge from hospital. This is an evidence-based booklet designed for patients having surgery for either disc prolapse or spinal decompression. Further details on the construction and content of the booklet have been previously reported [34].

#### Usual care

Patients randomised to the usual care control group will be managed according to the relevant surgeon's usual practice. The post-operative regimes of each surgeon will be documented and patients will be questioned via a self-completed questionnaire regarding any interventions received or advice sought.

### Outcome measures

The primary outcome measure is the Oswestry Disability Index (ODI, version 2.1), a disease-specific patient-completed questionnaire documenting function[56] of known validity and reliability [57], measured at the one year follow-up visit. This will be complemented by a series of secondary outcome measures. At baseline (the pre-operative assessment) and each follow-up point, simple 10 cm visual analogue scales (VAS) will be used to record least and usual back and leg pain, from which average values will be derived [58]. Measures of patient satisfaction will focus on the patient's satisfaction with the actual procedure undertaken and its outcome as opposed to satisfaction with the hospital's facilities, staff, etc. This will be assessed directly using a 5 point Likert scale ranging from 'complete improvement' to 'significant deterioration', and indirectly by comparing actual outcome with expected outcome. Expected outcome for pain and function will be assessed pre-operatively and at 6 weeks post-operation using 10 cm VAS, with subsequent satisfaction relating to each of these measures being assessed using similar VAS ranging from 'completely satisfied' to 'completely dissatisfied'[19]. Participants in the trial will be asked to complete the HADS [59], a well validated instrument for the assessment of anxiety and depression among patients in non-psychiatric hospital clinics at each assessment point. This will allow us to take pre-operative psychological status into account as a factor potentially affecting the outcome of surgery. In similar fashion, we will use the physical activity component of the Fear Avoidance Beliefs Questionnaire developed by Waddell et al[55] to take perceptions and expectations into account as possible influences on functional outcome. Information will also be collected on the timing and extent of any return to work, plus the nature of the participant's occupation, and on the timing and nature of any re-operations.

For the economic analysis we will collect data on costs and health-related quality of life (HRQOL) from patients in the trial. Costs will be collected from the perspective of the NHS, personal and social services (PSS) and patients and families. We will include costs for the following components where they are attributable to back pain: post-surgery rehabilitation; education booklet; hospital contacts (inpatient, day case, outpatient); primary care contacts (general practitioner, practice nurse, community nurse); and medications. We will distinguish between costs incurred by the NHS and by patients and families. Resource use data for each cost component will be obtained from patient diaries completed prospectively and collected at each post-operative review. These data will be combined with unit cost data from published national sources [60-62] to compute the costs for each patient in the trial. HRQOL will be measured using the EQ-5D, a validated, global measure of quality of life [63], which will also be measured at every post-operative review.

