The next step was to develop a post-operative intervention that was acceptable to both surgeons and patients. It was not possible to base this on current evidence as this was lacking, with respect to content and timing. At the initial workshop to develop this study, the surgeons were reluctant to discharge their patient directly into a rehabilitation class and the general consensus was that any form of rehabilitation class should start no sooner than 6 weeks post-operatively. Previous post-operative classes had either focused on stretching, resistance training, spine stabilisation exercises or mixed physiotherapy techniques [44,46,47,52]. With little agreement from these studies on what the key exercise content should be and a lack of evidence in the scientific literature the focus of the classes was to get the patient active, and it was decided to base the content on the style of Frost et al[53] Back to Fitness programme, but to extend these twice weekly classes over 6 weeks rather than 4. Based on the success of the Back Café concept described by Christensen et al [54] where patients benefited from meeting and discussing their surgery and progress with other patients, it was decided to include a discussion forum in the rehabilitation classes and for the classes to be of a rolling nature i.e. classes run continuously with patients joining the classes at their own allocated time rather than waiting for a new batch of classes to start. This facilitates patients at different stages of the post-operative journey sharing their experiences with others in the class. To incorporate all of these issues each class will last a maximum of one hour.

With the interventions in place it was possible to design an appropriate trial, the aim of which was to evaluate via a factorial randomised controlled trial, the benefits of a rehabilitation programme and an education booklet for the postoperative management of patients undergoing discectomy or lateral nerve root decompression, each compared with "usual care". The primary aim of this study is therefore, to determine if the long-term functional outcome of spinal surgery and patient satisfaction can be improved via either a systematic programme of post-operative rehabilitation or an educational booklet, and whether a combination of both is even more effective. A secondary objective is to assess whether or not such approaches are cost-effective.

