#### Rehabilitation Programme

Patients randomised to the rehabilitation arms of the trial will commence the programme 6 to 8 weeks following surgery. The programme will run for 6 weeks with patients attending for 1 hour twice a week. The classes will be run by an experienced physiotherapist, who will encourage patients individually to progress at their own pace. This structure allows new patients to join the programme at any time rather than in 'batches'. There will be a maximum of ten patients per class, located at the hospital where the surgery was performed.

The classes will be standardised using the principles outlined by Frost et al [53] and will include: general aerobic fitness work; stretching; stability exercises; strengthening and endurance training for the back, abdominal and leg muscles; ergonomic training; advice on lifting and setting targets; and self-motivation. Participants will be asked to undertake shorter (30 minute) sessions of exercise at home. The classes will have a cognitive therapy basis, and will include a group discussion/open session at the end of each class where patients can discuss any problems, worries and concerns they have with each other and the physiotherapist. Compliance with classes will be recorded on the basis of attendance, and a subgroup analysis will be conducted by proportion of classes attended. In addition the classes will be reviewed regularly to ensure a uniform quality and content.

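### Use of the trial's own classes and booklet is to be costed from patient diaries, although class attendance is already recorded and the booklet follows allocation

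*Protocol article*

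**What the plan says.** The economic part of Outcome measures restricts costing to back-pain-related use and lists these components: "post-surgery rehabilitation; education booklet; hospital contacts (inpatient, day case, outpatient); primary care contacts (general practitioner, practice nurse, community nurse); and medications". One rule then covers the whole list: "Resource use data for each cost component will be obtained from patient diaries completed prospectively and collected at each post-operative review". The next step is pricing: "These data will be combined with unit cost data from published national sources [60-62] to compute the costs for each patient in the trial". No exception is made for the two interventions that the trial itself delivers.

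The Rehabilitation Programme section describes a shared service: "The programme will run for 6 weeks with patients attending for 1 hour twice a week", and "There will be a maximum of ten patients per class, located at the hospital where the surgery was performed". The Background adds that "classes run continuously with patients joining the classes at their own allocated time rather than waiting for a new batch of classes to start". The programme section also provides a direct record of use: "Compliance with classes will be recorded on the basis of attendance, and a subgroup analysis will be conducted by proportion of classes attended". That record is tied to compliance and a subgroup analysis, and nothing links it to costing. The Educational Booklet and Trial Sample sections say that patients in the two booklet groups receive the booklet on discharge, so its use is known from allocation.

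**The concern.** A diary is a sensible source for general practitioner visits, outpatient contacts and medicines, which the trial team does not observe. It is a poor source for something the team delivers and records itself, for three reasons.

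- It relies on the patient to write down each class.
- It is collected only at reviews, so a patient who misses the relevant review may have attended classes that the costing never sees, although the attendance record holds them.
- It can count a patient's own visits but cannot say how many others were in the room. The cost of one attendance at a physiotherapist-led group depends on that number.

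What is at stake is the incremental cost of rehabilitation. It enters the three cost-effectiveness ratios and the budget impact analysis described under Proposed Analyses. The primary comparison on the Oswestry Disability Index (ODI) and the sample size are not touched.

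**Working it through.** The document states no rehabilitation cost, so there is no cost figure to reproduce. The check sets out what each source can supply and how strongly the cost depends on what the diary lacks.

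**1. Number of patients and classes.** The Trial Sample section gives a difference of 8 ODI points, SD 20, 90% power, two-sided alpha 0.05 and 23% loss.
- Per main-effect group: 2 × (20 × (1.960 + 1.282) / 8)² = 131.3, rounded up to 132.
- Allowing for loss: 132 / 0.77 = 171.4, rounded up to 172. Two groups give 344, as stated.
- So 172 patients are allocated to rehabilitation. Each is offered 6 weeks × 2 = 12 one-hour classes.

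**2. Which diaries carry the classes.** Classes start 6 to 8 weeks after surgery and last 6 weeks, so they end at weeks 12 to 14. Reviews fall at 6 weeks and 3, 6, 9 and 12 months, and 3 months is about week 13. The 3-month diary therefore holds most class visits, and the 6-month diary holds the last few for later starters. The relevant loss is of those two diaries. The stated 23% allows for loss at the one-year outcome, and the document gives no figure for 3 or 6 months.

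**3. What each source can show.**

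| Item | Patient diary | Trial's own record |
|---|---|---|
| Classes attended by a patient | Yes, if completed and returned | Yes, attendance record |
| Patients present at a class | No | Yes, if attendance is kept by session |
| Sessions run | No | Only if logged |
| Booklet received | Self-report | Allocation |

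**4. Dependence on class size.** With one physiotherapist per one-hour class, staff time per full course is 12 / (patients per class).

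| Patients per class | Physiotherapist hours per 12-class course |
|---|---|
| 10 (the stated maximum) | 12 / 10 = 1.2 |
| 5 | 12 / 5 = 2.4 |
| 2 | 12 / 2 = 6.0 |
| 1, or priced one-to-one | 12 / 1 = 12.0 |

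The span is tenfold.

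**5. Can the trial's own class size be worked out?** Mean trial patients per class = 172 × 12 × attendance / (sites × 2 × weeks). The document gives neither the number of class streams nor the period over which classes run. Assume one twice-weekly stream per site, 3 to 6 sites, 52 to 208 weeks and 50% to 100% attendance.
- Upper end: 172 × 12 × 1.0 / (3 × 2 × 52) = 2,064 / 312 = 6.6.
- Lower end: 172 × 12 × 0.5 / (6 × 2 × 208) = 1,032 / 2,496 = 0.4.

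This range is too wide to fix a cost. It shows only that class size has to be recorded and cannot be inferred.

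**The case against.** The strongest reply is that the costing has two steps. Diaries supply quantities and national sources supply prices, and class size belongs to the price. A published group-session cost, or an hourly staff cost divided by class size, would fit the text as written, and a well-kept diary can count classes correctly. The cited unit-cost sources are not at hand, so it cannot be said that attendances would be charged at a one-to-one rate. This stands. It rules out the claim that the rehabilitation cost will come out wrong.

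A reader might also infer a definite size of error: a severalfold understatement because trial classes would be far from full, or a fixed percentage bias from lost diaries. The document supports neither. The first needs an assumed number of streams and years, and an assumption that a full-class price will be used, which is stated nowhere. The second needs invented attendance rates and applies the one-year loss to diaries mostly due at 3 months.

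A further reply is that a journal article condenses a fuller plan, that nothing bars use of the attendance record, and that deterministic sensitivity analyses are already promised. This stands in part. How a unit cost is built may well be set out elsewhere. But the article does not merely leave the source of resource use open. It names diaries for every component, including two for which the trial holds better data. Sensitivity analysis on class size is also informative about the trial only if class size was recorded.

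Finally, dividing by trial attendance is not the only defensible base case. Half of the trial's patients are randomised away from classes, which may leave classes emptier than in routine use. That stands, and the point does not depend on either choice.

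**Conclusion.** The concern holds as a question of data source. The plan names a self-reported source, open to loss at reviews, for the trial's own classes and booklet, where attendance and allocation are direct. Rehabilitation may be mis-costed, but the amount and direction cannot be computed from the document. The range of 1.2 to 12 physiotherapist hours per course measures how much class size matters, assuming one physiotherapist per class and full attendance. It is not an estimate of error.

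The effect is confined to the secondary cost-effectiveness objective. That the classes cost more than the booklet is a fair inference from 12 supervised hours. That they dominate the whole cost difference between groups is not shown, because hospital contacts are costed too and their difference is unknown. This is a cheap improvement.

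**What to change.** In the economic paragraph of Outcome measures:

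- Take rehabilitation use from the class attendance record and booklet use from allocation. Keep diaries for hospital contacts, primary care contacts and medications.
- State that a class is costed from staff time, at national unit costs, shared over its attenders.
- In the deterministic sensitivity analyses and the budget impact analysis, report results at the class size observed in the trial and at the size expected in routine NHS use. Either may serve as the base case, provided the choice is stated in advance.

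The cost is a few lines of wording and a simple log of sessions run, with the number present at each. Attendance is already being recorded. If the full economic plan already costs the programme this way, one sentence saying so is enough.

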### Trial Sample

This trial has been approved by Hammersmith and Queen Charlotte's & Chelsea Hospitals Research Ethics Committee, with site approval for Ravenscourt Park Hospital, St Mary's Hospital, St Thomas' Hospital, Royal Free Hospital, Heatherwood and Wexham Park Hospital, and Charing Cross Hospital.

Eligible patients include those currently on the waiting list for spinal surgery with either (a) signs, symptoms and radiological evidence of lateral nerve root compression, that is, patients presenting with radicular pain with an associated neurological deficit or with neurogenic claudication (pain in the buttock, thigh or leg that improves with rest), or (b) lumbar disc prolapse, that is, patients with root symptoms and signs and MRI confirmation of lumbar disc herniation. Patients with any of the following will be excluded from participation in the trial; any condition where either the intervention or the rehabilitation may have an adverse effect on the individual; previous spinal surgery; spinal surgery where a fusion procedure is planned due to the unknown hazards of the activity programme for this type of surgery; pregnant women; inadequate ability to complete the trial assessment forms; any patient who is unable to attend the rehabilitation or the reviews or who is unsuitable for rehabilitation classes.

Written informed consent will be obtained from all patients and baseline assessment completed prior to surgery and randomisation into the trial. Patients will be notified of their randomisation following surgery. Those allocated to either the booklet-only group or the rehabilitation-plus-booklet group, will get the "Your back operation" on discharge (see details below).

The trial aims to recruit 344 patients into the trial with 86 patients in each of the 4 sub-groups. This figure was based on being able to detect a 20% relative improvement in the Oswestry Disability Index (version 2.1). We anticipate a mean ODI of 40 in the control group and 32 in the exercise group at 1 year, to have a 90% chance of detecting a between-group difference of 8 points on the ODI and declaring it statistically significant using a two-sided alpha= 0.05, requires a total of 344 patients. This calculation assumes a standard deviation of 20 in each group and allows for loss to follow-up of 23%, as found in earlier descriptive work [20].

### Proposed Analyses

Analyses will begin with a descriptive comparison of the trial groups before surgery to confirm that randomisation has produced groups that are balanced with respect to known confounders. This will include age, sex, type of surgery, ethnic background, marital status, body mass index, occupation type, work status and smoking status. Pre-operative scores on the primary and secondary outcomes will also be presented by group.

Full functional recovery from back surgery can be protracted, so the primary outcome of interest is the between-group difference in score on the ODI at one-year follow-up, based on intention-to-treat (modified to exclude patients recruited in error). Missing outcome data are expected because of this timeline. Multiple imputation under missing at random [64] will be used for patients with some follow-up but unmeasured one-year outcomes.

Groups will be compared via analysis of covariance, with adjustment for stratifying block using a linear mixed model. If assumptions appear violated, some transformation of the outcome will be taken such that assumptions appear sensible. If this fails, a non-parametric test will be used.

Parallel analyses will be performed for booklet vs. no-booklet and rehabilitation vs. no-rehabilitation, with the sample-size calculation given above applying to each of these. These calculations will be followed by an analysis which tests for an interaction of effect of the two interventions on the primary outcome.

We will check whether the same pattern of outcomes is apparent for patients undergoing lateral nerve root decompression and those undergoing discectomy, and for other subgroups defined by baseline body mass index, baseline HADS score, and single versus multiple anatomic levels of surgery. In addition to the analyses at one year, we will also compare the groups at 6 weeks (beginning of rehabilitation programme in the intervention group) and 3, 6, and 9 months.

The economic analysis will conform to recommended national guidelines [65]. We will undertake two analyses, a short-run analysis and a long-run analysis. In the short-run analysis the time horizon will be one year post-surgery and the analysis will be based on the data collected in the trial. In the long-run analysis we will extrapolate beyond the end of the trial using a de novo economic model to measure lifetime costs and benefits. Cost-effectiveness will be calculated as (1) the incremental cost per unit of improvement in functional outcome at one year, measured in terms of the primary outcome, (2) the incremental cost per quality-adjusted life year (QALY) gained at one year, and (3) the incremental cost per QALY gained over the lifetime. These measures summarise the extra costs and extra benefits of the interventions and can be used to assess whether or not they represent good value for money to the NHS. The economic analysis will include comprehensive deterministic and probabilistic sensitivity analyses to identify the areas of uncertainty in our analysis and the likely impact this will have on the results. We will also undertake a budget impact analysis to assess what the likely financial impact would be to the NHS if the interventions were rolled out nationally.

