## Methods/Design

### Trial Design

Function after spinal treatment, exercise and rehabilitation (FASTER) is a multi-centre, factorial, randomised, parallel group controlled trial using validated measures of outcome and with a parallel economic analysis. It involves recruiting and consenting patients with symptoms, signs, and radiological findings of either lateral nerve root compression or disc prolapse scheduled for surgery who will be randomised using a 2 × 2 factorial design to receive:

• Factor 1 - either a six-week programme of post-operative rehabilitation or the relevant surgeon's usual postoperative care, which includes clinical review and perhaps some very limited physiotherapy:

• Factor 2 - either an educational booklet ("Your Back Operation" see below), or the surgeon's usual advice.

This will create 4 groups; rehabilitation-only, booklet-only, rehabilitation-plus-booklet, and usual care only. Allocation to a group will be stratified by surgeon and surgical procedure and allocation will use random permuted blocks within strata. This ensures that each participating surgeon and both surgical procedures will have approximately equal numbers of patients allocated to the 4 groups. Treatment allocation will be concealed to avoid selection bias during recruitment. All patients will be assessed for functional ability, pain, and satisfaction pre-operatively and then at 6 weeks, 3, 6 and 9 months and 1 year post-operatively. This will be complemented by a formal analysis of cost-effectiveness. A summary is provided in figure 1.

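### Pre-operative ODI is not named as a covariate in the primary model; if the model is run as written, precision is given up at no saving

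*Protocol article*

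**What the plan says.** All references are to the Protocol article.

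- **Target of the analysis** (Proposed Analyses): "the primary outcome of interest is the between-group difference in score on the ODI at one-year follow-up". This is the one-year score itself and not change from baseline.
- **Model** (Proposed Analyses): "Groups will be compared via analysis of covariance, with adjustment for stratifying block using a linear mixed model". No other covariate is named.
- **Strata** (Trial Design): "Allocation to a group will be stratified by surgeon and surgical procedure and allocation will use random permuted blocks within strata".
- **Baseline data** (Trial Design): "All patients will be assessed for functional ability, pain, and satisfaction pre-operatively and then at 6 weeks, 3, 6 and 9 months and 1 year". The Trial Sample section adds that the baseline assessment is completed before surgery and before randomisation.
- **Stated use of baseline outcome scores** (Proposed Analyses): "Pre-operative scores on the primary and secondary outcomes will also be presented by group".
- **HADS**: the Outcome measures section says of its collection, "This will allow us to take pre-operative psychological status into account as a factor potentially affecting the outcome of surgery". In Proposed Analyses it appears once, in the plan to check the pattern of outcomes "for other subgroups defined by baseline body mass index, baseline HADS score, and single versus multiple anatomic levels of surgery".
- **Fear-avoidance score**: the Outcome measures section says it is collected "to take perceptions and expectations into account as possible influences on functional outcome". Proposed Analyses does not mention it.

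**The concern.** The article goes far enough to state the primary model and name an adjustment, yet that adjustment is only the stratum. Pre-operative ODI is the same instrument as the primary outcome. It is measured before allocation and so cannot be affected by treatment, and it is likely to be prognostic. It cannot enter through the outcome either, because the outcome is not a change score.

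A statistician who fitted exactly what is written would leave the variance explained by baseline ODI in the residual. Confidence intervals for both factors would be wider than they need be, and the estimate in the trial actually observed would carry whatever chance difference in pre-operative disability had arisen. The analysis section also opens with a check of baseline balance and names no covariates in advance. That leaves room for the covariate set to be chosen after the baseline table has been seen.

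**Working it through.** **Step 1. Reproduce the planned size.** Inputs from Trial Sample: difference 8 points (40 against 32), SD 20, two-sided alpha 0.05, power 90%, loss 23%.

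- n per side = 2 × (1.960 + 1.282)² × 20² / 8² = 131.3, rounded up to 132, so 264 evaluable.
- Inflated for loss: 264 / 0.77 = 343, or 132 / 0.77 = 172 per side, 344 in total.

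The stated 344 is reproduced from the raw SD of 20, with no term for a baseline correlation. Each factor is compared as 172 against 172.

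**Step 2. Power without baseline adjustment.** Evaluable per side = 344 × 0.77 / 2 = 132.4.

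- SE = 20 × √(2 / 132.4) = 2.46.
- Power = Φ(8 / 2.46 − 1.96) = 90.2%.

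**Step 3. Add pre-operative ODI.** Let r be the correlation between pre-operative and one-year ODI. The documents do not give it, so a range is assumed. Residual SD = 20 × √(1 − r²), and SE and power follow as in step 2. The difference detectable with 90% power is (1.960 + 1.282) × SE.

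| r (assumed) | Fall in residual variance | SE | Power for 8 points | Detectable at 90% |
|---|---|---|---|---|
| 0 | 0% | 2.46 | 90.2% | 7.97 |
| 0.3 | 9% | 2.35 | 92.7% | 7.60 |
| 0.4 | 16% | 2.25 | 94.4% | 7.30 |
| 0.5 | 25% | 2.13 | 96.4% | 6.90 |
| 0.6 | 36% | 1.97 | 98.3% | 6.37 |

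These gains are measured against no adjustment at all. The plan already adjusts for stratum. To the extent that surgeon and procedure explain the same variation as baseline ODI, the added gain is smaller, so the figures are best read as upper values for each r.

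**Step 4. Chance imbalance.** Let s be the baseline SD. The baseline difference between sides has SE s × √(2 / 132.4), and the slope of one-year on baseline ODI is r × 20 / s. For an imbalance of 1.96 SE, s cancels and the shift in the unadjusted estimate is 1.96 × 2.458 × r:

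- r = 0.3: 1.45 points (1.45 / 8 = 18% of the target);
- r = 0.5: 2.41 points (2.41 / 8 = 30% of the target).

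An imbalance this large, in either direction, arises in about 5% of trials. It is not an extra error on top of step 3. The unadjusted variance, 2.458², already contains the baseline share r² × 2.458², which is the part that adjustment removes.

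**The case against.** The strongest reply is that nothing has been excluded. An analysis of covariance normally has a covariate, and for a score taken before surgery and again at one year the obvious one is its baseline value. On that reading the stratum clause is an addition to an unspoken baseline term. Presenting baseline scores by group does not rule out using them in the model. The article is also a condensed account, and a full covariate list is commonly left to an analysis plan that is not shown here. This stands to the extent that a reader who concludes that the trial decided against baseline adjustment goes further than the text. It does not dispose of the point: the sentence that states the model names an adjustment and omits the covariate that would matter most.

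Three further inferences are tempting and are not supported.

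- **That omitting baseline ODI biases the result.** Chance imbalance after randomisation is not bias, and the unadjusted standard error allows for it. For missing one-year scores, the plan has multiple imputation for patients with some follow-up.
- **That the trial is underpowered without it.** The 344 gives 90.2% power from the unadjusted SD.
- **That HADS and fear-avoidance were promised as primary covariates.** The Outcome measures section says that they will be taken into account, and says nothing of the kind about ODI. It does not say that this means the primary model, and HADS does have a subgroup use. What remains is that the fear-avoidance score has a stated purpose and no named analysis.

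It is also fair to say that the gain is modest at the low end: at r = 0.3 it is under 3 percentage points of power.

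**Conclusion.** The point holds as one of precision. The primary model names only the stratifying block, and pre-operative ODI has no stated role beyond description. Followed literally, the plan forgoes a covariate already collected before randomisation. The cost is up to 9% to 36% of residual variance, or about 2 to 8 percentage points of power for an 8-point difference. That rests on an assumed correlation of 0.3 to 0.6, on the plan's SD of 20 and 23% loss, and on stratum not already absorbing much of the same variation. The loss is of precision and of accuracy conditional on the observed baseline. The planned comparison would still be valid and would keep its stated power. If baseline ODI was intended all along, the correction is only to say so. It is worth making either way, because it also settles the covariate before any baseline table is seen.

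**What to change.** State the primary model as one-year ODI on rehabilitation, booklet and pre-operative ODI, with stratum (surgeon by procedure) handled as now. Include pre-operative ODI in the imputation model so that it is consistent with the analysis model. For each secondary outcome, adjust for its own pre-operative value where one was measured.

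Place HADS and fear-avoidance in a pre-specified sensitivity analysis of the primary outcome. That gives the purpose stated under Outcome measures a matching analysis without requiring either score in the primary model.

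The cost is a sentence or two in the analysis section, one degree of freedom, and a short rule for any missing baseline questionnaire. No new data are needed and the sample size does not change.
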